## Abstract

**Background:**

Acute kidney injury (AKI) is a global public health challenge resulting in considerable morbidity and mortality. AKI on chronic kidney disease (CKD) (AKI on CKD, A on C) accounts for about a third of total AKI. For severe AKI grade 3, renal replacement therapy (RRT) should be implemented in time. However, the lack of recognized drug treatment method for AKI grades 1–2 is a crucial problem in clinic. Chuan Huang Fang (CHF) is a Chinese herbal formulation developed for the treatment of A on C from the Shanghai Municipal Hospital of Traditional Chinese Medicine. Our previous studies suggested that CHF might effectively protect renal functions of A on C patients. As a widely used antioxidant in clinic, reduced glutathione (RG) is reported to improve the clinical efficacy of high-flux hemodialysis (HFHD) in severe AKI patients recently. To address the crucial problem mentioned above, thus we design a new clinical protocol of CHF combining RG and try to evaluate the efficacy and safety of this protocol in treating patients diagnosed with CKD stages 2–4 complicated with AKI grades 1–2.

**Methods:**

This is a multicenter randomized controlled clinical trial. We intend to enroll 162 participants, and these participants will be divided into the RG group, the CHF group, and the RG + CHF group randomly assigning 1 : 1 : 1 principle. The RG group will be general treatments combining RG, the CHF group will be general treatments combining CHF, and the RG + CHF group will be general treatments combining RG and CHF. The duration of treatment will last two weeks. The primary evaluation outcome will be the change in the slope of serum creatinine (Scr) over 2 weeks. Secondary evaluation outcomes include changes in blood urea nitrogen (BUN), estimated glomerular filtration rate (eGFR), urinary AKI biomarkers (neutrophil gelatinase-associated lipocalin (NGAL), interleukin-18 (IL-18), gamma-glutamyl transpeptidase (*γ*-GT), etc.), traditional Chinese medicine (TCM) symptoms, inflammatory indicators, and oxidative stress indicators. Meanwhile, the vital sign indicators and adverse events (AEs) will be closely observed. These dates will be meticulously recorded and properly handled by investigators throughout the study. *Discussion*. This study will provide convictive research-derived data to evaluate clinical efficacy and safety of CHF combing RG for CKD stages 2–4 complicated with AKI grades 1–2 and provide an evidence-based recommendation for clinicians. The timely completion of this trial will provide a novel drug treatment method for A on C. This trial is registered with ChiCTR2100043311 and registered on February 9, 2021.

## 1. Introduction

AKI is defined as an abrupt decrease in kidney function, which encompasses both structural damage and functional loss [1]. According to 2012 Kidney Disease Improving Global Outcomes (KDIGO-2012) AKI definition [2], it is diagnosed by an increase in Scr to at least 0.3 mg/dl (26.5 *μ*mol/l) within 48 hours, or an increase in Scr to more than 1.5 times baseline during prior 7 days, or a urine volume decrease to less than 0.5 ml/kg/h for 6 hours. AKI is a global public health challenge [3], it is a severe complication caused by various critical diseases leading to considerable morbidity and mortality both in short term and long term [4, 5], and it implicates a great burden in sanitary costs [6]. A on C accounts for about a third of total AKI [7]. It is estimated that there are more than 13 million patients with AKI worldwide every year [8]. US statistical data indicate that the incidence of AKI is about 2100 per million [9]. A study on the clinical status of AKI in China points out that over 2 million patients are hospitalized with AKI, and about 700,000 patients died of AKI every year [10].

For severe AKI (grade 3), RRT should be implemented as soon as possible. It is reported that about 26.9% of patients with AKI require RRT eventually [11]. Current modalities of RRT for AKI include intermittent hemodialysis (IHD), continuous renal replacement therapy (CRRT), and peritoneal dialysis (PD). Also, sustained low-efficiency dialysis (SLED) has been put forward as an alternative RRT method and applied to clinical practice in many medical institutions worldwide [2, 12]. Recently, although AKI has attracted more and more attention and lots of related basic or clinical studies have been accomplished, there is still a lack of recognized drug treatment method for AKI grades 1–2 [13–15].

Studies have confirmed that oxidative stress injuries exist in the occurrence of AKI, and it plays an important role in affecting the prognosis of AKI [16]. At the same time, oxidative stress might induce inflammation by activating macrophages and complement systems, which would aggravate the potential kidney damage [16, 17]. Therefore, it is of great significance to pay more attention to the effect of oxidative stress in AKI.

Furthermore, several studies have shown that increasing pro-inflammatory biomarkers in AKI patients have a close connection with an elevated short-term mortality [18, 19]. Studies on AKI show that tumor necrosis factor-*α* (TNF-*α*), interleukin-6 (IL-6), and other cytokines have a significant meaning in the process of inflammation mediation [20]. During the early period of AKI, renal blood flow insufficiency might lead to sub-fatal renal tubular injury, and the inflammatory mediators generated by the injury might lead to vasoconstriction and aggravate ischemia. In addition, A on C may be the result of combined effects of abnormal hemodynamics, inflammation, oxidative stress, decreased prostaglandin synthesis, and increased synthesis of thromboxane in renal cortex [15, 21–23].

Based on the published data, during RRT unpopular period, Chinese doctors used to treat AKI with TCM methods [24]. CHF is a Chinese herbal formulation of [name] for treating A on C developed from the Shanghai Municipal Hospital of Traditional Chinese Medicine [25], and our previous small sample clinical studies suggest that CHF might effectively protect renal functions of A on C patients by preventing oxidant damage and inhibiting inflammation [15, 26, 27]. In the process of AKI, numerous oxygen-free radicals are generated, endogenous antioxidants are constantly consumed, and large numbers of inflammatory factors are released, aggravating kidney injury [28]. Reduced glutathione (RG) can effectively control the local inflammatory response, reduce the accumulation of reactive oxygen species in renal tissues, lower the level of inflammatory factors, and relieve oxidative stress in organs and tissues [29–31]. Recently, RG is reported to improve the clinical efficacy of HFHD in patients with severe AKI [32, 33]. Therefore, we plan to further optimize the original protocol, using CHF combining RG to form a new treatment method and finally carry out such a multicenter randomized controlled clinical trial on CKD stages 2–4 complicated with AKI grades 1–2 to evaluate the clinical efficacy and safety of this new method. The timely completion of this trial will provide a novel drug treatment method for A on C.

## 2. Methods

### 2.1. Objectives

This clinical trial is based on years of research studies in the early stage, which lays a solid foundation for successful completion. The aim was to evaluate the efficacy and safety of new treatment method CHF combining RG in treating A on C.

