### 2.4. Randomization and Blinding

A simple random method is adopted, and SPSS (version 21.0) software will be used by independent biostatisticians to generate random number sequences. Written informed consent should be signed immediately by himself/herself, agreeing to voluntarily enroll in the trial. Participants should be consented for randomization and participation. According to the sequence of enrolling in clinical observation, participants will be randomly numbered and divided into the RG group, the CHF group, and the RG + CHF group by investigators at 1 : 1 : 1 ratio. During randomization producer, sealed envelopes marked with sequential coding numbers will be adopted to keep allocation details, and group allocation should be kept blind to patients, biostatisticians, and investigators. As placebo is not used in the control group, it is not possible to be blind in the treatment. However, it is masked from staff performing all laboratory investigations.

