### 2.5. Interventions

Patients diagnosed with CKD stages 2–4 complicated with AKI grades 1–2 will be enrolled after signing written informed consents. They will be randomly divided into the RG group, the CHF group, and the RG + CHF group. To minimize potential loss and help participants conduct the trial smoothly, three group patients will receive study behavior and health education, and they will also be told possible risks and benefits, their rights and obligations, and how to handle an emergency situation. All patients will receive a low-salt, high-quality, and low-protein diet (protein intake 0.6–0.8 g/kg/d). Also, they will receive general treatments, whose purposes are to correct water, electrolyte, and acid-base balance disorders, control blood pressure, improve anemia, and correct renal bone diseases. Designed investigations will keep in touch with participants regularly and assist them to receive treatment and testing on schedule.

The RG group will be given RG 1.8 g added to 0.9% normal saline or 5% glucose 250 ml for injection, intravenous injection (IV), once per day for 2 weeks. The CHF group will be given CHF orally, twice per day for 2 weeks. At the same time, the concentrated solution of CHF will be given an enema, once per day for 5 days, and then rest for 2 days, 5 times in a week. The RG + CHF group will be the combination of the RG group and the CHF group, and intervention methods are the same as the above.

Pharmaceutical compositions of CHF are mainly as follows: prepared rhubarb (Zhida Huang), Ligusticum wallichii (Chuan Xiong), Codonopsis pilosula (Dangshen), Coptidis rhizome (Huanglian), Smilacis glabrae (Tufuling), etc. RG will be produced by Chongqing Yaoyou Pharmaceutical Co. Ltd., and CHF will be produced by Jiangyin Tianjiang Pharmaceutical Co. Ltd. Therefore, the quantity and quality of medicine can be effectively guaranteed.

Related examinations will be conducted and collected at baseline, every 1 week during treatment. Patient information will be recorded, and efficacy-related examinations, mechanism-related indicators, safety-related indicators, and drug management will be closely observed. Measured items and time points are listed in Table 3.

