### 2.7. Evaluation Criteria for TCM Syndrome Effect

Statistics are carried out according to the improvement of clinical symptom score with reference to the *Guidelines for Clinical Research of Chinese Medicine (New Drug)* [38], and the primary and secondary symptoms of spleen-kidney qi deficiency and toxicity stasis inter-combination syndrome will be classified as mild, moderate, and severe with 4, 8, and 12 points and 2, 4, and 8 points, respectively. The two total scores calculated by the measurement scale according to TCM symptoms for each patient will be summed up, and then, they will be used to calculate efficacy indicator (EI):  EI = (total symptom score before treatment -total symptom score after treatment)/total symptom score before treatment *X* 100%  EI is adopted to evaluate the treatment efficacy after treatment. Symptom improvement levels will be demonstrated in following categories: clinical control (EI ≥ 95%), significant effect (94% > EI ≥ 70%), and effectiveness (69% > EI ≥ 30%) to inefficacy (EI < 30%).

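### The three arms identify only what RG+CHF adds to each single drug; the objective and the anticipated conclusion are broader, and no required contrasts are named

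*Protocol article*

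**What the plan says.** **Arms.** The Abstract has participants "divided into the RG group, the CHF group, and the RG + CHF group randomly assigning 1 : 1 : 1 principle". It describes the arms thus: "The RG group will be general treatments combining RG, the CHF group will be general treatments combining CHF", with the third arm receiving both. Section 2.5 says of all patients: "Also, they will receive general treatments". Section 2.4 adds: "As placebo is not used in the control group, it is not possible to be blind in the treatment".

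**Status of the comparators.** The Introduction says "there is still a lack of recognized drug treatment method for AKI grades 1–2". It rests CHF on the group's own small clinical studies, and the recent clinical report it cites for RG concerns severe AKI treated with high-flux haemodialysis.

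**Objective and anticipated conclusion.** Section 2.1: "The aim was to evaluate the efficacy and safety of new treatment method CHF combining RG in treating A on C". The Abstract, and again the end of the Introduction: "The timely completion of this trial will provide a novel drug treatment method for A on C".

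**Hypothesis.** Section 2.9 expects Scr under RG+CHF to be lower than in each of the other two groups by more than 30 µmol/l (SD 44.43, power 0.90, α 0.05 one-sided, 20% dropout) and arrives at 54 per group, 162 in total.

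**Analysis.** Section 2.10 tests Scr with a one-way repeated-measures ANOVA, compares secondary outcomes between two groups, makes all tests two-sided and rules out additional analyses. Section 2.7 defines EI as each patient's percentage fall in symptom score, labels a fall of 30% or more as effective, and says "EI is adopted to evaluate the treatment efficacy after treatment".

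**The concern.** The objective asks whether the combination works in AKI on CKD. The arms answer a narrower question: whether the combination does better than either of its parts. The protocol does not present either part as an established treatment for AKI grades 1–2, so the comparison with general treatment, which would give the absolute effect, is not available at any sample size.

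This affects how each possible result can be read:

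- **No difference between arms:** the trial cannot tell whether all three regimens work or none does.
- **One contrast positive:** the added value of one component is shown and that of the other is not.
- **Both positive:** the combination is supported against each part.

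Only the third result supports the combination, yet nothing in the protocol says that both contrasts must succeed. The analysis named for Scr does not deliver them, and the promised conclusion does not depend on any result. The EI labels add to the risk, because they attach words for efficacy to a before-after change that also contains recovery under general treatment.

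**Working it through.** **1. What the arms identify.** Write G for general treatment.

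- RG+CHF minus RG = (G+RG+CHF) − (G+RG): the effect of adding CHF to RG.
- RG+CHF minus CHF = (G+RG+CHF) − (G+CHF): the effect of adding RG to CHF.
- RG+CHF minus G: not estimable, because no arm receives G alone.

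If mean Scr under RG+CHF is below both single-drug means, and at least one single drug is no worse than G, then RG+CHF is also better than G. The inference can fail only if both single drugs are worse than G, and the design cannot test that.

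**2. Reproducing the plan's sample size.** Inputs from 2.9: difference 30, SD 44.43, α 0.05, power 0.90, dropout 20%.

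- Take the two single-drug arms as equal and the combination 30 lower: means (0, 0, −30), average −10, deviations (10, 10, −20).
- SD of the means = √[(100 + 100 + 400)/3] = √200 = 14.14; f = 14.14/44.43 = 0.318.
- The three-group F test needs 42.65 per arm, so 43. 43/0.80 = 53.75, so 54 per arm and 3 × 54 = 162. This matches.
- A pairwise normal calculation gives 38 (one-sided) or 47 (two-sided), inflated to 48 or 59. Neither matches.

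The stated size therefore fits an overall test among three active arms.

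**3. What an overall test can mean.** Suppose RG+CHF equals RG, and both are 30 below CHF: means for CHF, RG and RG+CHF of (0, −30, −30), average −20, deviations (20, −10, −10). SD of the means = √[(400 + 100 + 100)/3] = 14.14, so f = 0.318 again. The F test has the same 0.90 power in a setting where the combination adds nothing to RG. Read literally, the one-way repeated-measures ANOVA in 2.10 is further away still, because its only factor is time. On either reading, a significant result does not show that the combination beats both single drugs.

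**4. Power to win both contrasts at the planned size.** 54 × 0.80 = 43.2, so 43 evaluable per arm.

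- Standard error of one contrast = 44.43 × √(2/43) = 9.58; 30/9.58 = 3.131.
- One contrast, two-sided: Φ(3.131 − 1.960) = 0.88. One-sided: Φ(3.131 − 1.645) = 0.93.
- The two contrasts share the combination arm, so their correlation is 0.5. The joint normal probability that both succeed is 0.80 two-sided and 0.88 one-sided. With t-tests instead of the normal approximation (by simulation) it is 0.79 and 0.88.
- Exactly one contrast significant when both 30 µmol/l effects are real, two-sided normal: 2 × (0.879 − 0.801) = 0.16.

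**The case against.** The strongest reply is that the comparison is already fixed. Section 2.9 states the hypothesis against each of the other groups, and the sample size follows from that configuration. Testing a combination against each component is a legitimate add-on design, and being unable to interpret a null result is a general limit of trials with active comparators. Section 2.10 speaks of comparisons between groups for secondary outcomes, which include TCM symptoms, and no within-arm test is planned. A condensed article may also leave detailed contrasts to an analysis plan.

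Most of this stands, and it confines the point to scope and wording. It does not remove the point. Section 2.1 does not carry the hypothesis of 2.9, the promised conclusion is unconditional, and 2.10 does more than stay silent: it names a test for Scr that does not address the hypothesis, refers to two groups in a three-arm trial, and excludes further analyses.

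A reader might infer four stronger things that the documents do not support:

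- **That the trial has no way of showing the combination to be effective.** Beating both single drugs is valid randomised evidence, subject to the assumption in step 1 of the working.
- **That the objective claims efficacy.** It says only that efficacy will be evaluated, and the closing Discussion is hedged. Only the sentence in the Abstract and Introduction is unconditional.
- **That spontaneous recovery threatens the planned 30 µmol/l comparison.** Recovery is common to randomised arms and is expected to cancel between them. It matters only if within-arm change is read as drug effect.
- **That a single positive contrast proves the other component useless.** That outcome has probability about 0.16 even when both effects are real.

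**Conclusion.** The point holds as a mismatch of scope. The randomised arms support conclusions about the added effect of RG+CHF over RG and over CHF. The objective and the unconditional sentence go further, and the protocol sets no rule that both contrasts must be won. The three-arm design and the stated sample size are not themselves in error.

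The size of the matter is the gap between the stated power of 0.90, which fits an overall test, and the power for the claim actually wanted: about 0.79 two-sided, as 2.10 specifies, or 0.88 one-sided, as 2.9 specifies. These figures assume a true difference of 30 µmol/l from each single drug, a common SD of 44.43, 43 evaluable patients per arm and unadjusted comparisons of Scr. Any extension to benefit over general treatment further assumes that the two single drugs are not both worse than it.

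**What to change.** 1. In 2.1 and the Abstract, state the objective as whether RG+CHF, on top of general treatment, lowers Scr at 2 weeks more than RG alone and more than CHF alone.
2. In 2.10, name the two between-arm contrasts and say that support for the combination requires both to be significant in its favour. Because both must succeed, each can be tested at the full 0.05 without a multiplicity adjustment. Add that if only one succeeds, the other component's added value is undemonstrated, not disproved.
3. In 2.7 and 2.10, say that Scr change and EI categories are interpreted only through differences between arms, and that within-arm changes are descriptive.
4. In the Abstract and Introduction, limit the promised conclusion to added benefit over each single drug at 2 weeks, conditional on the result.
5. In 2.9, report the power to win both contrasts at the planned size, under whichever sidedness is kept once 2.9 and 2.10 are reconciled.

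**Cost.** No change to arms, visits or number of patients. The headline claim becomes narrower, and the stated power for it falls from 0.90 to about 0.79 two-sided (0.88 one-sided).

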### 2.2. Study Design and Setting

This is a multicenter randomized controlled clinical trial in which participants will be recruited from the department of nephrology. Three hospitals are listed below: (1) Shanghai Municipal Hospital of Traditional Chinese Medicine; (2) Shuguang Hospital Affiliated to Shanghai University of Traditional Chinese Medicine; and (3) Minhang Branch of Yueyang Hospital of Integrative Chinese and Western Medicine Affiliated to Shanghai University of Traditional Chinese Medicine.

The design of this trial follows strict scientific clinical research methodology and complies with principles of *the Declaration of Helsinki* [34] and *the Guidelines for Good Clinical Practice* [35].

This trial is registered in the Chinese Clinical Trial Register (No. ChiCTR2100043311). The study flow chart is shown in Figure 1.

### 2.3. Participants

This trial plans to enroll potential eligible participants diagnosed with CKD stages 2–4 complicated with AKI grades 1–2 with spleen-kidney qi deficiency and toxicity stasis inter-combination syndrome. To encourage patients to participate in the trial, we will post recruitment posters in the above three hospitals and trial advertisements will also be accessed through study's Web page. Besides, we will pay attention to enrollment progress to make sure it could reach the target sample size.

#### 2.3.1. Diagnostic Criteria for AKI

According to KDIGO clinical practice guideline for acute kidney injury [2] and Quality Control Manual of Shanghai Nephrology Department [36], patients would be diagnosed with AKI if (1) increase in Scr by ≥ 0.3 mg/dl (≥26.5 *μ*mol/l) within 48 hours; or (2) increase in Scr to ≥1.5 times baseline during prior 7 days; or (3) urine volume <0.5 ml/kg/h for 6 hours. If patients cannot provide Scr baseline, clinicians can refer to Scr value within the last 3 months (no more than 1 year at the longest). If the value is still not available, patients should be required to repeat testing Scr within 24 hours to help diagnose AKI. KDIGO classification of AKI is as follows (Table 1).

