### 2.6. Outcome Measures

The primary evaluation outcome will be the change in the slope of Scr over 2 weeks. Posttreatment changes in BUN, eGFR, and urinary AKI biomarkers including urinary NGAL, IL-18, *γ*-GT, and TCM symptoms will be the secondary evaluation outcomes.

In addition to the secondary evaluation outcome, inflammatory indicators including TNF-*α* and IL-6 and oxidative stress indicators including heme oxygenase-1 (HO-1), malondialdehyde (MDA), and superoxide dismutase (SOD) will also be measured before and after treatment.

Safety outcomes and vital sign indicators (electrocardiogram, blood routine, urine routine, serum potassium, hemoglobin, etc.) will be recorded once before and 2 weeks after medication. Meanwhile, AEs will be closely observed, meticulously recorded, and properly handled by investigators throughout the study.

HCG: human chorionic gonadotropin; Scr: serum creatinine; BUN: blood urea nitrogen; eGFR: estimated glomerular filtration rate; TCM: traditional Chinese medicine; NGAL: neutrophil gelatinase-associated lipocalin: IL-18: interleukin-18; *γ*-GT: gamma-glutamyl transpeptidase; IL-6: interleukin-6; TNF-*α*: tumor necrosis factor-*α*; HO-1: heme oxygenase-1; MDA: malondialdehyde; SOD: superoxide dismutase.

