### 2.9. Sample Size Estimation

The sample size will be calculated according to the primary outcome of baseline Scr change. Based on previous studies and literature reports [26, 30], the mean value of Scr was 160.39 *μ*mol/l, and the standard deviation was 44.43 *μ*mol/l. We thus hypothesize that Scr for CHF combing RG group would be significantly lower than the other two groups by more than 30 *μ*mol/l. It is calculated using the sample size estimation software PASS (version 15.0.3) to achieve test efficacy 1–*β* = 0.90 and significant difference *α* = 0.05 (one-sided test). Considering 20% drop rate, the estimated sample size for randomization will be 54 cases in each group for a total of 162 cases.

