### 2.10. Statistical Analysis

The principal analysis will be conducted on a full analysis set (FAS), which consists of participants randomly allocated into two groups. Participants completing and complying well with the study protocol without major violation will be referred to the per-protocol population. All participants taking test drugs will be enrolled in safety analysis and conform with the ITT principle.

For non-normally distributed variables, mean ± standard deviation or median will be brought to describe continuous variables. Categorical variables will be presented in the form of numbers and percentages. The difference in Scr will be tested using the one-way ANOVA with repeated measures. The secondary outcomes will be compared between two groups using the independent-samples Student's *t*-tests for normally distributed continuous data and using Pearson's chi-square test (or Fisher's exact test if cell count <5 in any cell) for categorical data. Two-sided tests will be used for all statistical tests, and *P* < 0.05 will be considered statistically significant. SPSS (version 21.0) software will be used to carry out statistical analysis by a biostatistician not involved in the study. No additional analyses or interim analysis will be performed.

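### The primary Scr test is in effect an unadjusted change-score comparison; adding week-0 Scr, and the pre-AKI reference Scr where available, would buy precision at almost no cost

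*Protocol article*

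**What the plan says.** **Outcome and test.** Section 2.6 states: "The primary evaluation outcome will be the change in the slope of Scr over 2 weeks". Section 2.10 states: "The difference in Scr will be tested using the one-way ANOVA with repeated measures". It names no covariate or stratification factor and adds: "No additional analyses or interim analysis will be performed". Table 3 marks renal function at week 0 and week 2 only. Randomisation in section 2.4 is simple and unstratified.

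**Reference creatinine.** Section 2.3.1 offers three routes to an AKI diagnosis: a rise of at least 26.5 μmol/l within 48 hours; "increase in Scr to ≥1.5 times baseline during prior 7 days"; or "urine volume <0.5 ml/kg/h for 6 hours". A patient without a baseline value may be judged against one from the last 3 months, or at most a year old. Failing that: "If the value is still not available, patients should be required to repeat testing Scr within 24 hours to help diagnose AKI". Table 1 grades AKI by the ratio to this reference value (1.5–1.9 for grade 1, 2.0–2.9 for grade 2) or, for grade 1, by the 26.5 μmol/l rise. Table 3 does not list the reference value as a data item.

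**Two meanings of one word.** In section 2.3.1 and Table 1, *baseline* is the pre-AKI value. In Table 3 it is the week-0 visit. Section 2.9 says: "The sample size will be calculated according to the primary outcome of baseline Scr change". There it can only sensibly mean change from study entry.

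**The concern.** How far creatinine can fall in two weeks depends largely on how far it had risen. Two patients who enter at 200 μmol/l, one with a reference of 170 and the other of 100, have 30 and 100 μmol/l to recover. A change-score comparison removes each patient's stable level but leaves this spread in the error term. Enrolment covers CKD stages 2–4 and AKI grades 1–2 (section 2.3.4), so week-0 Scr alone cannot separate a high reference with a small rise from a low reference with a large one.

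What is at stake is the width of the confidence interval for the primary comparison and the power of its test. The ambiguous word adds a practical risk: an analyst told to adjust for baseline Scr could pick either quantity.

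**Working it through.** **1. The plan's own sample size.** Inputs from section 2.9: difference 30, SD 44.43, power 0.90, α 0.05, dropout 20%. The stated number reproduces as an unadjusted three-group ANOVA F test with means (0, 0, −30):

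- Grand mean −10; squared deviations 100 + 100 + 400 = 600.
- λ = n × 600 / 44.43². At n = 43, λ = 25,800 / 1,974.0 = 13.07 and power is 0.903; at n = 42 it is 0.895.
- 43 / 0.80 = 53.75, hence 54 per group and 162 in total.

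The planning therefore makes no allowance for covariates. (A two-group calculation gives 48 per group one-sided or 59 two-sided, so it does not reproduce 54.)

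**2. Why the test is a change-score comparison.** I read the test as including the arm-by-time term, which is needed to compare arms. With two time points, that test is algebraically a one-way ANOVA on week-2 minus week-0 Scr. This relies on Table 3. The text of section 2.5 speaks of weekly examinations; if Scr were also taken at week 1 the identity would no longer hold, but there would still be no covariate.

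**3. Spread in recoverable Scr under the plan's criteria.** Take an entry Scr of 160.39, the section 2.9 mean, for illustration (its time point is not stated). Room to recover = entry − reference.

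| Rise at entry | Reference | Room |
|---|---|---|
| +26.5 μmol/l | 133.9 | 26.5 |
| 1.5 × reference | 106.9 | 53.5 |
| 1.9 × | 84.4 | 76.0 |
| 2.0 × | 80.2 | 80.2 |
| 2.9 × | 55.3 | 105.1 |

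The spread is about fourfold (105.1 / 26.5 = 4.0) among patients admitted on a creatinine criterion.

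**4. Size of the gain, by simulation.** Every input here is an assumption. The example setting is: log-normal reference with mean 115 and SD 40; entry ratio 1.15–1.9 (grade 1) or 2.0–2.9 (grade 2, 30% of patients); rise at least 26.5 and entry below 353.6; recovery averaging 60% (SD 30%) of the rise; 5% noise at week 2; 7% noise in the reference; none missing. Power is for a two-sided 0.05 t test with 43 per arm and noncentrality 30 / (SD × √(2/43)).

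| Analysis | SD | Noncentrality | Power at 30 |
|---|---|---|---|
| Change score | 41.4 | 3.36 | 91% |
| Week-0 Scr as covariate | 34.1 | 4.08 | 98% |
| Week-0 and reference Scr | 31.0 | 4.49 | 99% |

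- Week-0 adjustment cuts the variance by 1 − (34.1/41.4)² = 32%.
- The reference value cuts it by a further 1 − (31.0/34.1)² = 17%.

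**5. Noisy or missing reference values.** In the same setting, with a missing-indicator term, the further reduction is:

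- about 8% with 15% noise and 30% missing;
- about 3% with 25% noise and 50% missing (SD about 33.5, power at 30 still 98%).

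Across settings with reference mean/SD of 100/25, 115/40 or 140/55, 10% or 30% grade 2, and recovery averaging 0.4–0.8 (SD 0.2–0.5), it runs from about 2% to 50%. The low end comes from very variable recovery: 100/25, 10% grade 2 and recovery 0.4 (SD 0.5) gives about 2%.

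**6. Cross-check on the plan's own SD.** Let R² be the assumed share of the variance that adjustment removes, so residual SD = 44.43 × √(1 − R²). At 43 per group, F-test power rises from 0.903 (R² = 0) to 0.931 (R² = 0.10; SD 42.15) and 0.976 (R² = 0.30; SD 37.17). With R² near 0 there is no gain.

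**The case against.** Four objections carry weight.

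- **Not every patient has a reference value.** A reader might infer that eligibility screening yields a pre-AKI Scr for all. Section 2.3.1 does not support that. The urine-volume route needs no creatinine, the 48-hour rise need not start from a stable pre-AKI value, the 24-hour repeat is taken during the episode, and a substitute may be a year old. This stands and limits the gain.
- **No bias.** A reader might also infer that treating unlike patients alike distorts the arm comparison. Allocation is random, so leaving out a prognostic covariate costs power and leaves chance imbalance unadjusted, but the comparison stays valid. This stands.
- **The reference value adds little at the planned effect.** At 30 μmol/l it adds about one percentage point of power or less beyond week-0 adjustment; most of the gain comes from week-0 Scr. A smaller difference would make it look larger (at 20 μmol/l the three analyses give 60%, 77% and 84%), but 20 is not a figure in the protocol. This stands.
- **A SAP may name covariates.** It may, and the sentence excluding additional analyses does not clearly bar covariates from the primary model. But the protocol does name its primary test, and as written that test is unadjusted. The point is therefore fair as a suggested improvement and does not amount to an error in the plan.

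**Conclusion.** The point holds as a cheap gain in precision. As written, the primary analysis uses neither week-0 Scr as a covariate nor the pre-AKI reference Scr, while the eligibility criteria allow about a fourfold spread in recoverable creatinine at a given entry value.

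In the example setting, power at 30 μmol/l with 43 per arm goes from about 91% to 98% with week-0 Scr, and to 98–99% with the reference value as well. The ranking of the three models is secure in large samples, because each added covariate can only lower residual variance or leave it unchanged. The amounts are not secure: the documents give no correlation between either value and the outcome, and the simulated patients enter at about 199 μmol/l (SD 63) against the 160.39 (SD 44.43) of section 2.9.

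The documents do not support saying that the trial is invalid or underpowered because of this omission, or quoting any single figure for the loss. The double use of *baseline* needs no simulation and should be corrected in any case.

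**What to change.** 1. Make the primary comparison an ANCOVA of week-2 Scr on arm with week-0 Scr as covariate. With week-0 Scr in the model, analysing week-2 Scr or the change gives the same arm difference, so the outcome remains a two-week change.
2. Add the pre-AKI reference Scr where available. Record its value, date and source on the CRF before allocation is revealed, since treatment is open.
3. Pre-specify one missing-value rule: if there is no pre-AKI value within the one-year limit already in section 2.3.1, set the covariate to a constant and include a missing indicator. Do not substitute a 24-hour repeat value taken during AKI, which is a different quantity.
4. Reserve *baseline* for one of the two values, for example week 0, and call the other the pre-AKI reference Scr throughout.

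The cost is one CRF entry (value, date, source) and up to three model terms, with no extra test or patient. The downside is that some reference values will be old or missing, which shrinks the gain from step 2 but leaves the gain from step 1 intact.
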